### Primary outcomes

#### Isotonic strength and endurance

Isotonic maximal strength (1 repetition maximum (1RM)) and endurance test (maximum number of repetitions performed at 45% of 1 RM) will be performed during leg press, shoulder flexion, calf press and chest press using a procedure earlier used in an untrained middle-aged population [33]. All RM tests will be separated by a 5-min rest period.

All tests will be performed using exercise equipment that are available at each included center. Leg-press, chest-press and calf press tests will be performed using available weight machines and the shoulder flexion test will be performed using free weights. The tests will be performed in order to individualize progression and to determine the effects of the training performed after the 8-week intervention period. 1RM is defined as the maximum load able to be lifted with good technique through the full range of motion (ROM) [34]. The structure of all 1RM testing is designed so that a 1RM could be achieved in 3–5 attempts. All 1RM test will be preceded by a warm-up of 10 repetitions, using a light load, performed from the start position to the end position in each exercise. The start loading for 1RM testing will correspond to a perceived resistance of 50–70% of 1RM with gradual increases in each trial until 1RM is achieved. The rate of the gradual increase in load is dependent on the participant’s self-perceived capacity and 3–5 min of rest will be used between trials. Lastly, the settings and load of each exercise trial will be noted in the protocol.Leg press will be tested with the participants placed in a seated leg-press machine, adjusted so that the range of movement (ROM) of the knee joint will be from 90° flexion to full extension without discomfort in hip or ankle joints. Feet will be positioned shoulder-width apart and fully in contact with the surface during the whole ROM and arms held crossed over the chest. The start position for the test will be with the knee joint in 90° flexion. The placement of the feet will be noted so that the pre- and post-intervention testing will be done in the same positionShoulder flexion will be tested using dumbbells, performed while seated on a bench with backrest (120° hip angle) with both feet on the floor. Using one dumbbell in each hand, the participant starts with arms hanging towards the floor, then raises the dumbbell, thumbs pointing upwards, with a fully extended elbow using flexion of the shoulder in the sagittal plane to a 120° shoulder flexion, defined by when the participant can see their own elbow, and returns to the start position. A string will be attached in front of the participant to help participants as well as evaluators to ensure that the movement will be performed in the whole ROMCalf press will be tested using the same machine as for the leg press. The feet are placed so that when the participant’s knees are fully extended the legs are aligned with the applied force from the machine. The starting position will be with fully extended knees and the whole sole of the feet on the surface and the end position will be at full individual plantar flexion. The placement of the feet will be noted so that the pre- and post-intervention testing will be done in the same positionChest press will be tested with the handlebars placed at mid-sternum height and while the participant grips the handles with the elbows at 90° flexion at sternum height. The back should lie be firmly on the backrest and both feet on the floor. When the participant reaches full extension in the elbows, the end position of the movement will be considered reached

For the multiple RM (limb-muscle endurance) test, the settings and starting positions from the 1RM test will be used. Our multiple RM is defined as the maximum number of repetitions able to be lifted with a good technique through the full ROM at an intensity corresponding to 45% of 1 RM [34]. In order for training specificity, an upper limit of 60 repetitions on the multiple RM test will be used at baseline testing. If a participant exceeds 60 repetitions on a multiple RM test at baseline, the test will be redone with a higher resistance. A maximum of three tests will be performed. Test order will be pre-determined: (1) leg-press, (2) shoulder flexion, (3) calf press and (4) chest press. Warm-up will be one set of 10 repetitions using 50% of the resistance to be used in the multiple RM test. The pace will be controlled by the participant’s breathing.

### Secondary outcomes

#### Functional performance

Walking performance will be evaluated by the endurance shuttle walk test (ESWT) performed in accordance to guidelines, reported in meters or seconds [35, 36]. The incremental shuttle walk test (ISWT) will be performed in order to determine the correct walking speed for the ESWT. The ISWT continues until the participant can no longer continue or cannot keep up with the required pace. The maximum duration of the test is 20 min [35]. The ESWT is a derivative of the ISWT, where patients walk for as long as possible at a predetermined percentage of maximum walking performance as assessed by the ISWT [36]. One test is sufficient to obtain a reliable measure [35]. The ESWT are responsive to changes with interventions in patients with COPD [37].

During the 60STS, participants will be instructed to fully stand up and sit down as fast as possible, as many times as possible within 60 s. Arms will be held folded across the chest with feet remaining in full contact with the floor. The number of repetitions performed within 60 s will be collected. Chair height will be 48 cm or low enough to allow both feet to be in full contact with the floor. The test is reliable, valid and responsive for measuring functional exercise capacity for people with COPD [38, 39].

The UULEX test is performed seated. Start position of the test is seated, with the plastic bar (0.2 kg) held with both hands at shoulder width, resting on the proximal parts of the thighs of the participant. Participants will then be asked to raise it from hip to the UULEX eight-level chart for 2 min at the first level and thereafter, 1 min at each level with a cadence of 30 movements per min. If a patient reaches the highest level, the plastic bar will be replaced by a heavier one every min. There are five different bar weights (0.2, 0.5, 1, 1.5, 2 kg) and participants will continue on the highest level until symptom limitation [40].

#### Isometric quadriceps strength and endurance

In addition to isotonic measurements of muscle strength and endurance, we will also perform isometric measurements, since the different techniques (isotonic versus isometric) might differ with regard to clinical relevance and responsiveness to training [41].

Isometric testing will be performed either using a Biodex Multi-Joint System 3 or 4 (Biodex Corp., Shirley, NY, USA) or a fixed-strain gauge (Biopac System inc, Goleta, CA, USA), depending on the availability of system at each respective center.

After a warm-up of two to three submaximal contractions, five maximal trials will be performed with each contraction sustained for 5 s. One-minute rests will be given between repeated trials to minimize muscle fatigue. Quadriceps maximal voluntary contraction (MVC) torque will be recorded in Newton meters (Nm) for each contraction. Thus, for strain-gauge measurements the Nm will be calculated by dividing force in Newtons by the length of the lever arm. The peak of the two best reproducible contractions (within a 5% coefficient of variation) will be reported as the test result.

After a 15-min rest period, the muscle strength test will be followed by an isometric measurement of quadriceps endurance. Participants will be instructed to maintain a tension representing 60% of their MVC until exhaustion. A computer screen will serve as a feedback mechanism to help subjects maintain the determined submaximal tension. Subjects will be strongly encouraged to pursue until tension drop under 50% MVC. The time to fatigue, defined as the time at which the isometric contraction reached 50% MVC, will be used as a measure of muscle endurance.

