### Secondary objectives

2.To compare the effect of NLPRT and RT on (1) functional performance measured with the endurance shuttle walk test (ESWT), the 60-s Sit to Stand Test (60STS) and the Unsupported Upper Limb Exercise Test (UULEX), (2) isometric quadriceps muscle strength and endurance, (3) health-related, disease-specific quality of life (HRQoL), (4) dyspnea and (5) the proportion of responders for each of these variables (a response being defined as an improvement that is larger than the known minimal detectable change/or minimal important difference for a given variable).*Hypothesis*: NLPRT will result in a greater gain on functional performance, isometric quadriceps muscle endurance, HRQoL dyspnea, as well as a larger number of responders while effects will be similar with regard to isometric muscle strength at week 93.To determine the feasibility of NLPRT compared to RT on attendance rate, duration, satisfaction, drop-outs as well as occurrence and severity of any adverse events.*Hypothesis*: that NLPRT will be feasible to the same extent as RT over 8 weeks of training4.To determine the responsiveness of isometric quadriceps strength and endurance measurement to NLPRT and RT.*Hypothesis*: isometric quadriceps muscle strength measurements will be highly responsive to NLPRT as well as RT represented by a standardized response mean (SRM) > 0.80, while quadriceps endurance measurements will be highly responsive to NLPRT but moderately responsive to RT (SRM 0.50 > 0.80) at week 95.To explore the intramuscular adaptations of NLPRT compared to the intramuscular adaptations of RT*Hypothesis*: NLPRT will result in a larger increase in muscle capillarization as well as in the activity of citrate synthase (CS) and lactate dehydrogenase (LDH) compared to RT at week 9

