### Statistics

The primary analyses will be an intention-to-treat analysis (including all participants randomized) in addition, a complete case population (participants with complete outcome measurements independent on adherence to intervention), and a per-protocol analysis (defined as at least 80% overall attendance rate as well as no exacerbations during the last 2 weeks prior to follow-up assessment) will be performed. Missing data will be imputed in the intention-to-treat analysis using multiple imputation assuming data is missing at random conditional on participant severity of disease and history of exacerbations. This is because severity of disease and history of exacerbations are known risk factors for future exacerbations and may affect adherence to the training protocol [28].

Mixed models will be used for analysis of data with individuals at level 1 and center at level 2. Estimates of effect sizes will be computed using Cohen’s *d* (*d* = difference in group means/error SD within). Calculated as the difference between predicted means from the final mixed-effects model for a given pair of groups divided by the estimated within-group error SD in the model with the estimated value of $$ 2{\sigma}_e^2 $$, where $$ {\sigma}_e^2 $$ is the residual variance. To judge the quality of the model we will analyze the residuals. For responsiveness, values of 0.20, 0.50 and ≥ 0.80 correspond to small, moderate and large responsiveness, respectively [50].

We will consider two-sided *p* values < 0.05 as statistically significant for the primary outcomes without correction for a multiplicity of tests assuming that each test represents an independent function based on the specificity principle of training [26]. Relationships between parameters will be evaluated using Pearson correlation coefficients. The strength of the correlation coefficients will be categorized as low (0–0.25), moderate (> 0.25–0.50), strong (> 0.50–0.75), very strong (> 0.75). Pre-planned subgroup analyses are differences between men and women. Statistical analysis will be performed using the statistical package SPSS 23.1.

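### The strain-gauge rule divides force by lever arm, which does not give torque in Nm; if applied literally it would distort pooled isometric quadriceps strength, a secondary outcome.

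*Protocol article*

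**What the plan says.** All of this is in the protocol article.

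- **Quantity and unit** (Isometric quadriceps strength and endurance): "Quadriceps maximal voluntary contraction (MVC) torque will be recorded in Newton meters (Nm) for each contraction".
- **Strain-gauge rule** (same paragraph): "Thus, for strain-gauge measurements the Nm will be calculated by dividing force in Newtons by the length of the lever arm". No other section corrects this or gives another formula.
- **Devices** (same section): a Biodex System 3 or 4 "or a fixed-strain gauge (Biopac System inc, Goleta, CA, USA), depending on the availability of system at each respective center". The article does not say which of the four centers use the strain gauge. It gives no lever-arm length and no unit for it.
- **Role of the outcome** (Secondary objectives): the arms are compared on "2) isometric quadriceps muscle strength and endurance". A separate objective concerns responsiveness, with a hypothesized standardized response mean (SRM) above 0.80 for isometric quadriceps strength in both arms.
- **Analysis** (Statistics): "Mixed models will be used for analysis of data with individuals at level 1 and center at level 2". Cohen's d is to be computed from the model's predicted means and residual variance.

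**The concern.** The sentence is an operative calculation rule, and it is dimensionally wrong. Newtons divided by metres give N/m, whereas the required quantity in Nm is Newtons multiplied by metres. Under the stated rule, of two participants producing the same force, the one with the longer lever arm gets the lower value.

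The mix of devices adds to the problem. If every center made the same scaling error, much of it would cancel in standardized or relative measures. Here some centers may record true Nm from a Biodex while others record a rescaled number under the same label, and both enter one analysis. A center-level intercept removes a difference in level. It does not remove a multiplicative difference, which also scales the changes, the treatment effects and the residual spread.

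At stake are the between-arm comparison of isometric strength in absolute units, the Cohen's d built on the pooled residual variance, and the SRM hypothesis for isometric strength.

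**Working it through.** The plan gives no figure to reproduce, so the check is dimensional and then a direct ratio.

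**Inputs.** The rule F/L, the unit Nm, the two device types and the pooled model come from the article. The lever arm L, the force F, the split of centers and the effect sizes below are assumptions for illustration only.

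**1. Units.** Torque = F × L, in N × m = Nm. Stated rule = F / L, in N/m. The two agree numerically only at L = 1 m.

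**2. Size of the error.** (F/L) ÷ (F × L) = 1/L², with L in metres. If L is entered in centimetres, the ratio is 1/(100 L²).

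| Assumed L (m) | L entered in metres | L entered in centimetres |
|---|---|---|
| 0.25 | 16.0 times too high | 6.25 times too low |
| 0.30 | 11.1 times too high | 9.0 times too low |
| 0.35 | 8.16 times too high | 12.25 times too low |
| 0.40 | 6.25 times too high | 16.0 times too low |
| 0.50 | 4.0 times too high | 25.0 times too low |

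Example: F = 400 N and L = 0.35 m. True torque is 400 × 0.35 = 140 Nm. The stated rule returns 400 / 0.35 = 1142.9.

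**3. Role of lever arm.** Take two participants with the same true torque of 120 Nm. At L = 0.30 m the rule gives 120 / 0.30² = 1333; at L = 0.40 m it gives 120 / 0.40² = 750.

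**4. What does not change.** Let force rise from 350 to 400 N at a constant L = 0.35 m. Percent change is 14.3% under either formula. Absolute change is 50 × 0.35 = 17.5 Nm correctly, and 50 / 0.35 = 142.9 under the stated rule.

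**5. Effect of pooling.** Assume four equal centers, two on strain gauge, L = 0.35 m for everyone (factor 8.16), and the same true effect and SD at every center.

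- *Mean difference.* A true 10 Nm difference pools to (2 × 81.6 + 2 × 10) / 4 = 45.8.
- *Share of the sum of squares.* 8.16² = 66.6, so strain-gauge centers supply 2 × 66.6 / (2 × 66.6 + 2) = 98.5%.
- *Cohen's d.* The pooled difference is (1 + 8.16)/2 = 4.58 times the true one. The pooled residual SD is √((1 + 66.6)/2) = 5.81 times the true one. So d is about 4.58 / 5.81 = 0.79 of its true value. This ignores the smaller term that arises because the effect now differs between centers.
- *SRM.* Suppose the true SRM is 1.0 at every center (mean change 1, SD 1). The pooled mean change is 4.58. The pooled variance is (1 + 66.6)/2 + ((8.16 − 1)/2)² = 33.8 + 12.8 = 46.6, so the SD is 6.83 and the SRM is 4.58 / 6.83 = 0.67, below the hypothesized 0.80. To reach 0.80, the true SRM s must satisfy 4.58 s / √(33.8 + 12.8 s²) = 0.80, which gives s of about 1.30.

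**The case against.** The strongest reply is that this is a slip of the pen for multiplying. The preceding sentence fixes the quantity as torque in Nm, the article says assessors have previous experience of the outcomes, and a reading near 1143 would stand out beside Biodex values. This is plausible, and nothing in the article shows that any value was computed by the literal rule. The harm to the data is therefore conditional. The error in the text is not, and a protocol that asks for strictly standardized procedures across centers should not carry a wrong formula.

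Several stronger readings are tempting but not supported:

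- **That strain-gauge centers will be 6 to 11 times too high.** That range assumes L of about 0.30 to 0.40 m entered in metres. The article gives neither the length nor its unit, so even the direction is not fixed.
- **That responder counts would be driven by noise crossing a threshold in Nm.** The article gives no Nm threshold. Its only responder examples are 177 s for the ESWT and three repetitions for the 60STS.
- **That correlations with biopsy measures are compromised.** Biopsies come from Umeå and Quebec only, and the article does not say whether either uses a strain gauge.
- **That the main result or the arm comparison is biased.** The primary outcomes are isotonic 1RM and repetitions, and do not use this formula. Randomization is stratified by center, so mis-scaling does not by itself favor an arm.
- **That isometric endurance is also wrong.** It is a time to fatigue at percentages of the participant's own MVC, and a constant rescaling leaves it unchanged.

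Within a single-device center the SRM would also be largely preserved. The damage to the responsiveness objective arises when absolute changes are pooled across devices.

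**Conclusion.** The stated rule is wrong as written: it yields N/m, contradicts the Nm it claims to produce, and reverses the role of lever-arm length. This follows from the text alone.

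The numerical size depends on the assumed L and its unit, as tabulated above, and on the rule being applied literally. Under those conditions the pooled absolute change, residual variance, Cohen's d and SRM for isometric quadriceps strength would be distorted. The pooled figures further assume two of four equal centers on strain gauge and L = 0.35 m; under that assumption a true SRM of 1.0 would fall below the hypothesized 0.80.

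The consequence is confined to absolute values of one secondary outcome and what is computed from them. This is a certain error with a near-zero-cost correction, not a threat to the trial's primary conclusions.

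**What to change.** 1. Reword the sentence so that strain-gauge torque in Nm is force in Newtons multiplied by lever-arm length in metres.
2. Require the lever arm to be recorded for each participant and held constant before and after training.
3. Check any strain-gauge values already entered, since the article reports recruitment under way at submission, and recompute them if the literal rule was used.

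The cost is one corrected sentence plus a data check. Recomputation is trivial where raw force and lever arm were kept. The article implies that both are used but does not say that both are stored. Where only the result of the division and L survive, true torque is that result multiplied by L² (L in metres, if the division also used metres).

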#### HRQoL

The self-administered version of the chronic respiratory disease questionnaire (CRQ-SA) [42] will be used to assess HRQoL. The CRQ is a widely used disease-specific questionnaire to assess symptoms of people with COPD. The CRQ is valid and responsive to treatment [43], and has previously been used to evaluate the effects of resistance training [31, 44].

#### Dyspnea

The Borg CR10 will be used to quantify the level of dyspnea during exercise training and tests while general dyspnea in daily life will be evaluated using the dyspnea subscale of the CRQ.

#### Number of responders

The total amount of responders, i.e., defined as a response over the known minimal detectable change/or minimal important difference for included test(s), will be determined and compared. For example, the minimal important difference after rehabilitation is suggested to be 177 s for the ESWT [45] and three repetitions for the 60 STS [46].

#### Feasibility

Feasibility of the training programs will be assessed and compared between groups from the attendance rate, duration, satisfaction, drop-outs as well as occurrence and severity of any adverse events.Attendance rate will be evaluated by calculating the number of attended sessions divided by total number of sessionsDuration of exercise sessions will be evaluated by measuring the time taken to complete an exercise session, including the 5-min mandatory rest periods before and after the exercise sessionPatient satisfaction with the exercise regimens will be recorded by adapting an existing patient satisfaction questionnaire previously used for single-legged cycling [47].The number of drop-outs will be collected and compared across resistance regimensInformation about adverse events will be collected for both exercise protocols. Two independent pulmonologists and one physiotherapist whom will not be involved in the study will evaluate the adverse events. The severity of the adverse events will be assessed and rated into four different categories: (1) minor and temporary, (2) serious symptoms (potential risk of severe injury or life threatening), (3) manifest injury or disease and (4) death, as previously used [48]. An adverse event rate will be calculated for each patient as the total number of sessions during which any adverse events occurred divided by the total number of attended sessions

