## Training interventions

Participants will be randomized to either NLPRT or RT of leg press, shoulder flexion, calf press and chest press exercises (three times per week for 8 weeks). The following will be similar for both the NLPRT and the RT groups.All exercises will be performed using training equipment available at each participating center. Leg press, chest press and calf press exercises will be performed using available weight machines and the shoulder flexion exercise will be performed using free weightsExercise order will be pre-determined: (1) leg press, (2) shoulder flexion, (3) calf press and (4) chest press. This exercise order will be used in order to alternate between lower and upper-limb exercises and between multiple- and single-joint exercises. All exercises will be performed bilaterallyRest between exercises will be standardized to 4 min and all exercises will be performed using dynamic repetitions with both concentric and eccentric muscle actions. The speed of motion in each exercise will be controlled by the breathing of the participant, we expect a moderate exercise velocity, i.e., 1–2:1–2 s in the concentric and the eccentric phase, respectivelyAll sessions will be supervised and conducted by local professionals using a group format, with approximately two to four participants per groupEach session will span approximately 60 min including a mandatory 5-min rest before and after the training sessions. During this time, oxygen saturation, heart rate, dyspnea and general fatigue (rated on the Borg revised category ratio 0–10 scale (Borg CR10) [23]), will be collectedDyspnea, limb-muscle fatigue and exertion ratings on Borg CR10, the later defined as “how heavy the exercise felt,” will be collected immediately after each set of exerciseExercise volume for each training session = (number of repetitions per set × sets per exercise × exercises per session) will be reportedNew 1 repetition max (RM) and multiple RM tests will be performed three times during the 8-week intervention period (after session 5, 10 and 15) in order to optimize exercise loadings. If a 1-RM test is lower than the prior 1 RM or if there is a mismatch between calculated training load from the new 1 RM and training load during the previous week, the higher training load will be used and a new test will be performed prior to the next training session to minimize the impact of alterations in daily fitnessNo general warm-up will be performed prior to sessions but a specific warm-up set of 15 repetitions using a load corresponding to 30% of 1RM prior to each exercises will be performed within the NLPRT and RT sessions

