#### Participant safety

Reasons for immediately stopping an outcome tests or training session for people with COPD will include the following: (1) chest pain, (2) intolerable dyspnea, (3) leg cramps, (4) staggering, (5) diaphoresis and (6) pale or ashen appearance [27]. The assessors and instructors are trained to recognize these problems and to deliver the appropriate intervention. Further, this will be reported as an adverse event. If a participant experiences pain/discomfort from the exercising limb during training no progression will occur even if the participant reaches other requirements for progression in the NLPRT or RT group, respectively. If pain prohibits execution of an exercise, this specific exercise will be removed.

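### The only adverse-event rate the protocol defines cannot register events outside training sessions, so it does not fully measure the promised comparison of any adverse events

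*Protocol article*

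**What the plan says.** The Feasibility section of the protocol article says that the programs will be "compared between groups from the attendance rate, duration, satisfaction, drop-outs as well as occurrence and severity of any adverse events". The third objective, under Secondary objectives, has the same scope.

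The section then takes the items in turn. For adverse events it provides for collection in both arms and for evaluation by people outside the study. On grading it states: "The severity of the adverse events will be assessed and rated into four different categories". The scale runs up to death. The item closes with its one occurrence measure, a rate worked out patient by patient: "the total number of sessions during which any adverse events occurred divided by the total number of attended sessions". Drop-outs are a separate item, counted and compared by arm.

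The Participant safety section gives one list of stopping reasons for tests and training alike: "Reasons for immediately stopping an outcome tests or training session for people with COPD will include the following". After the list it adds: "Further, this will be reported as an adverse event". A stop during an outcome test is therefore a reportable adverse event.

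**The concern.** The objective covers any adverse event, whereas the defined rate covers only events that happen during a session. Three kinds of event fall in the gap:

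- an exacerbation at home;
- pain or injury that shows itself between sessions;
- a stop in a week-9 outcome test.

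The protocol itself expects the first of these. Its Statistics section treats exacerbations as something that may affect adherence, and it makes freedom from a recent exacerbation a condition of the per-protocol set.

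The hypothesis for this objective is that the periodized program will be as feasible as the traditional one. The arms differ in load, volume and progression, so a difference in events between sessions cannot be ruled out. A rate that scores those events as zero could make the arms look alike when they are not. That error would favour the stated hypothesis.

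**Working it through.** The protocol states no numerical adverse-event rate, so there is no figure to reproduce. The check applies the definition to example participants. The event patterns are assumptions chosen to show how the formula behaves and are not data from the protocol.

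**Inputs**

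- Planned sessions, from Training interventions: "three times per week for 8 weeks", so 3 × 8 = 24.
- Rate for a patient, from Feasibility: r = s / a, where s is the number of sessions with at least one event and a is the number of sessions attended.

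**What counts as a session.** The Feasibility section uses attended sessions for the attendance rate and exercise sessions for duration. The safety section names the two settings separately: "Reasons for immediately stopping an outcome tests or training session for people with COPD". Procedure speaks of test visits. The natural reading is therefore training sessions. The repeat strength and endurance tests after sessions 5, 10 and 15 are a borderline case that the text does not settle.

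**Results**

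| Example participant | s / a | Rate |
|---|---|---|
| Completer, no event | 0/24 | 0% |
| Completer, one in-session event | 1/24 | 4.2% |
| Completer, three events in the same session | 1/24 | 4.2% |
| Completer, one event between sessions or at the week-9 tests | 0/24 | 0% |
| In-session event at session 6, then drop-out | 1/6 | 16.7% |
| Event between sessions after session 6, then drop-out | 0/6 | 0% |
| Randomised, no session attended | 0/0 | undefined |

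Three things follow.

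1. An event outside a session gives the same score as no event, whether or not the person then leaves.
2. Three events in one session score the same as one.
3. An in-session event that ends participation is counted, and it gives a higher rate than the same event in a completer (16.7% against 4.2%).

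**The case against.** The strongest reply is that the rate is not the arm comparison. The protocol names the occurrence and severity of any adverse event as a between-group comparison, and nothing says the session rate replaces it. Events are collected in both arms without a stated restriction to sessions, and drop-outs are compared separately. The per-protocol definition presupposes that exacerbations are recorded. A per-session rate is also a coherent tolerability measure under a feasibility heading.

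Much of this stands, and it rules out several stronger readings that a reader might infer:

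- **That out-of-session events are left out of the arm comparison.** The text does not say so; the general comparison is worded to include them.
- **That events leading to drop-out are missed.** Only those outside a session are. A participant who leaves after an out-of-session event would still appear in the drop-out count.
- **That the share of time outside sessions shows the share of events missed.** About 24 hours of training in 8 × 7 × 24 = 1,344 hours is 1.8%. That compares time, not risk, and the protocol gives no distribution of events.
- **That people with few sessions dominate the result.** This would need the per-patient ratios to be averaged, and no summary method is stated.
- **That all outcome-test events matter here.** Allocation follows the baseline tests, so baseline events cannot reflect the assigned program. Only the week-9 tests are at issue.

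The reply does not close the gap. The general sentence gives no counting unit, time window or denominator, and the only measure defined beneath it cannot register these events. A drop-out count does not show which departures followed an adverse event.

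**Conclusion.** The point holds in a limited form. The protocol fixes one occurrence measure for adverse events, and that measure is narrower than the objective it serves. It scores an event outside a training session as 0% where the same event inside one would score 4.2% in a completer, and it counts several events in one session once. How far this would shift the comparison between arms cannot be estimated, because the protocol gives no expected event frequencies.

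The conclusion rests on reading sessions as training sessions. If test visits were meant to count, week-9 stops would enter the rate, but events between sessions still would not. The matter should be corrected. It does not threaten the primary outcomes, and it does not show that adverse events will go uncollected.

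**What to change.** For the between-group comparison, define the measure to match the objective:

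1. Count every adverse event from randomisation to the end of the week-9 assessments, including events between sessions and at the week-9 tests.
2. In all randomised participants, report by arm and severity category the number with at least one event, and the total events per participant-week of follow-up.
3. Keep the session-based ratio as a tolerability measure, pooled by arm: total sessions with an event divided by total sessions attended. Pooling also removes the undefined 0/0 for someone who attends no session.
4. State whether events in the repeat strength and endurance tests during the program count as in-session.

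A count model is optional. With 64 participants and four severity categories, events may be too sparse to fit one, and the tabulation may be enough.

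The cost is small. Events are already to be collected and independently graded, and participants attend supervised sessions three times a week, so no extra visits are needed. The downside is slightly more recording, mainly of events between sessions, and a slightly longer table.
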